# Dose-response relationship of core-specific sensorimotor interventions in healthy, well-trained participants: study protocol for a (MiSpEx) randomized controlled trial

**DOI:** 10.1186/s13063-018-2799-9

**Published:** 2018-08-06

**Keywords:** Sensorimotor training, Perturbation, Exercise, MiSpEx

## Abstract

**Background:**

Core-specific sensorimotor exercises are proven to enhance neuromuscular activity of the trunk, improve athletic performance and prevent back pain. However, the dose-response relationship and, therefore, the dose required to improve trunk function is still under debate. The purpose of the present trial will be to compare four different intervention strategies of sensorimotor exercises that will result in improved trunk function.

**Methods/design:**

A single-blind, four-armed, randomized controlled trial with a 3-week (home-based) intervention phase and two measurement days pre and post intervention (M1/M2) is designed. Experimental procedures on both measurement days will include evaluation of maximum isokinetic and isometric trunk strength (extension/flexion, rotation) including perturbations, as well as neuromuscular trunk activity while performing strength testing. The primary outcome is trunk strength (peak torque). Neuromuscular activity (amplitude, latencies as a response to perturbation) serves as secondary outcome.

The control group will perform a standardized exercise program of four sensorimotor exercises (three sets of 10 repetitions) in each of six training sessions (30 min duration) over 3 weeks. The intervention groups’ programs differ in the number of exercises, sets per exercise and, therefore, overall training amount (group I: six sessions, three exercises, two sets; group II: six sessions, two exercises, two sets; group III: six sessions, one exercise, three sets). The intervention programs of groups I, II and III include additional perturbations for all exercises to increase both the difficulty and the efficacy of the exercises performed. Statistical analysis will be performed after examining the underlying assumptions for parametric and non-parametric testing.

**Discussion:**

The results of the study will be clinically relevant, not only for researchers but also for (sports) therapists, physicians, coaches, athletes and the general population who have the aim of improving trunk function.

**Trial registration:**

German Clinical Trials Register, ID: DRKS00012917. Registered on 22 August 2017.

**Electronic supplementary material:**

The online version of this article (10.1186/s13063-018-2799-9) contains supplementary material, which is available to authorized users.

## Background

One main function of the trunk muscles is the compensation of external forces and unexpected loads in order to ensure stability of the body. Consequently, compensation of external loads ensures the stability and performance of the body during daily life as well as in dynamic, high-intensity activities [1–3]. Trunk stability, led by neuromuscular activity, is required to control trunk motion during repetitive (dynamic) loading situations and to avoid overloading. Importantly, reduced trunk stabilization, mainly characterized by an increased muscle response time, higher co-contraction and an altered muscle activity pattern, could contribute to overload and injury [4, 5]. Consequently, inadequate neuromuscular control during dynamic loading is discussed as an explanatory model in back pain etiology [6, 7]. Therefore, great emphasis has been placed on the importance of trunk stability, especially in situations requiring compensation of (unexpected) high loading induced, e.g., by perturbations [5, 8]. Potential factors underlying back pain have been discussed, including repetitive micro traumas and insufficiency of the muscle-tendon complex based on inadequate postural and neuromuscular control, reduced maximum trunk-strength capacity and trunk-muscle fatigue during dynamic loading [9]. Hence, optimizing neuromuscular core stability is considered beneficial for protection against sudden, repetitive and excessive overloading of the trunk [2–4, 8].

Exercise interventions are proven to improve trunk stability [10–12]. Strengthening exercises have been applied and shown to be effective. Moreover, alongside the focus on strengthening exercises, additional training methods preferring neuromuscular, sensorimotor training or combinations thereof have been shown to be effective, too [10–12]. However, the dose-response relationship between sensorimotor training using exercises under unstable and/or perturbed conditions and trunk function still remains unclear. Especially for sensorimotor training, the benefits in terms of maximum eccentric and concentric trunk strength and peak torque as well as neuromuscular activity adaptation in sudden, dynamic trunk-loading situations have not been systematically highlighted.

In a pilot feasibility study (unpublished material, RCT (MiSpEx), German Clinical Trials Register No. DRKS00004977) including *n* = 750 participants, it could be shown that a core-specific sensorimotor exercise program (four exercises; nine sessions over 3 weeks; three sets of 10 repetitions per exercise) led to a significant increase in trunk function (strength gain) and pain reduction compared to a control group (no intervention). A compliance analysis revealed that more than one session per week (at least six sessions over 3 weeks) were necessary to achieve significant enhancement (function/pain reduction). In a recent Cochrane review on motor control exercises for non-specific low-back pain, Saragiotto et al. [10] summarized that the exercise programs’ duration ranged between 20 days and 12 weeks, with a number of sessions ranging from one to five per week. However, the exact determination of a valid dose-response relationship describing a reduced exercise amount and intensity necessary to improve trunk function remains unclear. Hence, the purpose of this study is to explore and compare the effect of three different 3-week (home-based) sensorimotor training programs in comparison to an evident control intervention, each varying the amount and intensity of training. Outcomes are maximum isokinetic trunk strength and trunk response (neuromuscular activity) to sudden, high-intensity trunk loading in healthy, normal, active adults.

## Methods/design

### Study design and flow

The study is designed as a single-blind, four-armed, randomized controlled trial with two identical measurement days (M1/M2), in which participants are allocated to either the experimental groups or the control group. All groups, interventions as well as control, receive 3 weeks of core-specific sensorimotor training organized in different home-based protocols. Potential participants are screened and examined by a sports medicine physician before baseline assessment and randomization to the groups to determine eligibility. Participants’ maximum trunk strength and trunk response to sudden, high-intensity trunk loading is assessed at baseline and after the 3-week intervention phase (Figs. 1 and 2; Additional file 1). All adverse events will be monitored and reported.

**Fig. 1 Fig1:**
[figure not shown]
Trial flowchart

**Fig. 2 Fig2:**
[figure not shown]
Standard Protocol Items: Recommendations for Interventional Trials (SPIRIT) Figure: schedule of enrollment, interventions and assessments

### Participants

#### Recruitment, screening and informed consent

Healthy, well-trained participants are recruited via the university outpatient clinic (e.g., athletes receiving annual health check-ups), flyers (displayed at the university and sports facilities) and existing contacts with training groups at the Olympic Center. Inclusion criteria are defined as age between 18 and 50 years and at least weekly training. Acute infection, pregnancy, any illness that contraindicates exercise, as well as acute or chronic back pain serve as exclusion criteria. Before voluntary participation, all subjects read and sign their written informed consent. The University’s Ethics Commission has approved the study (No. 23/2017).

### Intervention

#### Therapy flow

Trained and experienced physio- or sports therapists instruct the participants on all training programs (intervention and control; home-based). Following the randomization, both intervention and control group participants are scheduled for a guided training session, followed by a 3-week, home-based individual training.

#### Intervention groups and control group

Control and intervention group participants are instructed to perform six training sessions during the 3-week, home-based training phase. However, the number of exercises and sets per exercise vary between the control group and all intervention groups. Training frequency and number of exercises per group are detailed in Table 1.

**Table 1 Tab1:** Intervention and control groups: details of training frequency and number of exercises per group

Group	Intervention	Total amount of sessions	Total time per session	Number of exercises	Sets per exercise
Control group C	MiSpEx protocol	6	30 min	4 (rowing, side plank, bird dog, standing balance)	3
Intervention group I G I	Better than nothing	6	20 min	3 (rowing, side plank, bird dog)	2
Intervention group II G II	Half-way done	6	10 min	2 (side plank, bird dog)	2
Intervention group III G III	Only once	6	5 min	1 (side plank)	3

The control group performs a standard protocol consisting of four different sensorimotor core-specific exercises (Table 2). All four exercises will be performed with three sets of 10 repetitions each, with a minimum of 30 s rest in between sets (unpublished material, RCT (MiSpEx), German Clinical Trials Register No. DRKS00004977, [13, 14]). In between exercises, a 2-min break (self-controlled) is allowed. The exercises are commonly described as: (1) bird dog; (2) deadlift/rowing; (3) single-leg stance and (4) side planks. Two of the exercises, bird dog and side plank, are dedicated to directly training the core-stabilizing and/or core-surrounding muscles while the other two exercises, deadlift/rowing and single-leg standing balance, are considered to impact the core indirectly by means of the upper and/or lower extremities. To account for possible side effects, side plank and single-leg stance are always performed at ten repetitions each side.

**Table 2 Tab2:** Exercise details: for each exercise, level (1–3), surface (stable/unstable) and description including perturbation are provided

	Exercise 1: bird dog		Exercise 2: deadlift/rowing		Exercise 3: single-leg standing balance		Exercise 4: side planks	
					
Exercise Level	Task	Perturbation	Task	Perturbation	Task	Perturbation	Task	Perturbation
Level 1 (1st week)	Hand and knee stance diagonal arm and leg: from body center upwards (horizontal) on unstable surface	Terra Band Instability	Rowing in ball stance on stable surface	Terra Band	Unipedal stance plus hip abduction on stable surface	Terra Band	Knee on ground; hip up/down	Instability
Level 2 (2nd week)	Hand and feet stance: bending, stretching a leg on stable surface	Terra Band	Rowing in ball stance on unstable surface	Terra Band Instability	Unipedal stance plus hip abduction and leg extension on stable surface	Terra Band	Knee on ground; hip up/down on unstable surface	Ball task (roll ball to the wall and catch it back)
Level 3 (3rd week)	Hand and feet stance: bending, stretching a leg on unstable surface	Terra Band Instability	One-handed rowing on stable surface	Terra Band	Unipedal stance plus hip abduction and leg extension on unstable surface	Terra Band Instability	Legs stretched, hip fixed upwards on stable surface	Ball task (roll from hand to feet and vice versa)

Intervention group I (G I) performs three exercises (rowing, side plank, bird dog) with two sets of 10 repetitions for each exercise, with a minimum of 30 s rest in between sets. In between exercises, again a 2-min break is held. Intervention group II (G II) performs two exercises (bird dog, side plank) with two sets of 10 repetitions for each exercise and a 2-min break in between exercises. The training program of intervention group III (G III) consists of one exercise (side plank) with three sets of 10 repetitions (30 s rest in between sets).

In all intervention groups, all exercises comprise three different levels. To enhance the efficacy of the exercises, perturbations are integrated into all exercises in all three intervention groups with the aim of increasing the difficulty and, therefore, the demands on the trunk-muscle activity. Details of the four different exercises and the levels including perturbation are presented in Table 2.

#### Therapy monitoring

During the (home-based) intervention phase, a standardized training log is completed by each participant documenting each training session. The progression of the 3-week intervention is explained and demonstrated during a guided training session prior to the start of the home-based intervention.

### Randomization procedure and blinding

After inclusion, participants are randomized into either one of the three interventions or the control group by the study coordinator. The randomization order follows the study inclusion order. The randomization list is generated using a computer-based algorithm (www.randomization.com). All investigators (measurement team) other than the study coordinator and the therapist are blinded. Participants are instructed not to communicate their group allocation to other participants or study staff.

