## Discussion

The main purpose of this study is to analyze the dose-response relationship between core-specific sensorimotor intervention programs of different training intensities and trunk function, represented by maximum strength capacity, sudden loading compensation and neuromuscular activity. Therefore, a feasible study protocol based on a single-blind randomized controlled design is used.

All training programs, control and all intervention groups, consist of core-specific sensorimotor exercises [10, 12, 23]. Moreover, additive sensorimotor perturbation will be applied to one (control group) and all exercises (all intervention groups) to enhance the efficacy of neuromuscular activity while exercising [24–26]. In a pilot study, Mueller et al. [25] showed that the use of additional perturbations during core-specific sensorimotor exercises was superior for enhancing trunk neuromuscular activity. Higher EMG amplitudes might indicate higher exercise intensity, but additional functional benefits and long-term effects still need to be investigated. Although convincing evidence exists for the relevance of sensorimotor exercises and their combination with additional perturbations to enhance core stability and trunk function, fundamental information on the dose-response relationship is rather sparse.

A main strength of the planned intervention programs is the overall short exercise duration as well as the low usage of resources in the home-based intervention [10]. This cost-effective intervention might be feasible for the transfer to the general population and/or elite athletes.

One main limitation in the trial presented here is the blinding of the participants. To keep the risk of bias to a minimum, all involved investigators are blinded to the group allocation.

In summary, the presented trial provides further insight into the dose-response relationship for core-specific sensorimotor exercises and the definition of a minimum dosage required to improve trunk function. In addition, the efficacy or non-efficacy of the sensorimotor exercises targeting neuromuscular factors like strength and neuromuscular activity will be evaluated in detail.

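### The target population is described inconsistently, and the analysis as described has no training-level factor although entry spans recreational exercisers to Olympic Center athletes; the cost is precision and unclear scope, not bias

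*Protocol article*

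**What the plan says.** - **Population.** The title uses the word well-trained, and so does the recruitment section: "Healthy, well-trained participants are recruited via the university outpatient clinic". The aim, at the end of the Background, is set "in healthy, normal, active adults".
- **Entry rule.** "Inclusion criteria are defined as age between 18 and 50 years and at least weekly training". There is no upper limit and there are no training bands. The exclusions concern illness, pregnancy and back pain.
- **Sources.** Athletes attending the outpatient clinic for check-ups, people answering flyers at the university and sports facilities, and "existing contacts with training groups at the Olympic Center".
- **Allocation** (Randomization procedure and blinding). The study coordinator uses one computer-generated list. "The randomization order follows the study inclusion order". No stratum or block is named.
- **Analysis** (Statistical analysis). Between-group differences in the M1-M2 change are tested by one-way ANOVA, with a two-way ANOVA for dependent samples given as an example for hypothesis testing. No covariate or training-level factor is named. There are 20 participants per group, and the article says no power analysis was done.
- **Intended use** (Discussion). The trial is meant to help define the minimum dose that improves trunk function. A paragraph on short duration and low cost says the intervention might be "feasible for the transfer to the general population and/or elite athletes".

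**The concern.** A minimum dose is a statement about a population, and the article gives three descriptions that do not coincide: well-trained people, normal active adults, and anyone who trains weekly. The entry rule does not by itself deliver the cohort in the title. It admits both a once-a-week exerciser and a squad athlete, so a pooled result would be hard to assign to either.

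The second part is statistical. If training level is related to the gain over three weeks, it adds variance to the change score and can be unevenly spread over arms of 20. It is knowable at enrolment, yet as described neither the allocation nor the model uses it. With a sample size not based on a power calculation, avoidable loss of precision deserves attention.

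**Working it through.** **Inputs from the article:** four arms of 20, so 4 × 20 = 80 participants; alpha 0.05 (taken as two-sided); one list; change-score ANOVA without a training factor. The 20 per group cannot be reproduced, because no effect size, SD or power is given.

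**Assumptions (not in the article):** athletes make up 30-50% of the 80; athletes and non-athletes differ in mean gain by δ = 0.5 or 1.0 within-group SD. The true dose difference used for the power figures is 0.8 SD for one pair of arms, without Bonferroni adjustment.

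**Step 1. Chance imbalance.** With K athletes among 80 and random allocation to four arms of 20, the counts a and b in two given arms have probability C(20,a) · C(20,b) · C(40,K−a−b) / C(80,K). Summing over |a−b| ≥ 5 gives the figure for a given pair. The four-arm version of the same formula gives the largest-minus-smallest count.

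| Athlete share (K) | Given pair differs by ≥5 of 20 | Most extreme pair differs by ≥5 of 20 |
|---|---|---|
| 30% (24) | 0.12 | 0.41 |
| 40% (32) | 0.15 | 0.47 |
| 50% (40) | 0.16 | 0.49 |

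The mean absolute gap for a given pair is about 2.3-2.5 participants.

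**Step 2. What a gap does to a contrast.** A gap of 5 of 20 is 0.25. It shifts the realised contrast by 0.25 × δ, that is 0.125 SD (δ = 0.5) to 0.25 SD (δ = 1.0).

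**Step 3. What the trial can detect.** At 80% power with 20 per arm, the detectable difference is √(2/20) × (z for alpha + 0.842):
- unadjusted: 0.316 × (1.960 + 0.842) = 0.89 SD
- Bonferroni for 3 comparisons: 0.316 × (2.394 + 0.842) = 1.02 SD
- Bonferroni for 6 comparisons: 0.316 × (2.638 + 0.842) = 1.10 SD

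The shift in step 2 is small beside these.

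**Step 4. Cost in power.** If training level is ignored, the variance of the gain becomes 1 + p(1−p)δ², where p is the athlete share. Power is Φ(0.8 / (SD × √(2/20)) − 1.960).
- Training level accounted for (SD = 1): Φ(2.530 − 1.960) = 71.6%.
- δ = 0.5: variance 1.053 at p = 0.3 and 1.063 at p = 0.5; power 69.4% and 68.9%, a loss of 2.2 to 2.7 points.
- δ = 1.0: variance 1.21 at p = 0.3 and 1.25 at p = 0.5; power 63.3% and 61.9%, a loss of 8.3 to 9.7 points.

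**Step 5. Type I error.** In 20,000 simulated null trials (50% athletes, δ = 1.0, one-way ANOVA without adjustment), 5.05% were rejected at the 5% level.

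**The case against.** Several stronger readings are tempting, and the article does not support them.

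- **That the comparison is biased.** A reader might infer that an arm that happens to receive more athletes must show a smaller gain whatever its dose. Its gain also depends on its dose, and valid randomization leaves the comparison unbiased on average. Step 5 shows that the error rate holds.
- **That the list is unstratified.** The article does not say so. One list taken in inclusion order points that way, but a condensed article may omit blocks or strata. This stands as a caution; a sentence on how the list was built would settle it.
- **That training level governs room for gain.** No passage states this, and nothing is said about season phase. The size of the link is an assumption, and if it is zero the power argument falls away.
- **That imbalance is the rule.** The 0.41-0.49 is for the most extreme pair picked after the fact; for a given pair it is 0.12-0.16.
- **That one dose is claimed for everyone.** The Discussion remark is hedged and concerns the feasibility of transfer.

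It is also fair to say that a broad entry rule and simple randomization of 80 people are legitimate choices. Results by stratum would rest on about 6-10 athletes per arm (30-50% of 20), too few to judge dose in athletes alone. None of this removes the mismatch in the population wording, or the fact that the analysis as described leaves an enrolment factor unused.

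**Conclusion.** The point holds in two parts. First, the title and recruitment section, the aim and the entry rule describe different populations, so it is unclear to whom a minimum dose would apply. This needs no assumption. Second, as described, neither allocation nor analysis uses training level. The consequence is lost precision: roughly 2-10 points of power for a true difference of 0.8 SD, the upper end requiring a full 1.0 SD difference in gain between athletes and non-athletes. No figure in the article is contradicted and no stated test is invalid. The change is worth making because it is cheap and the sample is small, not because the dose comparison would otherwise be unsound.

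**What to change.** 1. Record training level (squad athlete or recreational) at enrolment. Include it as a prespecified factor, alongside baseline torque, in the between-group model. The power is recovered in the model, so this step is useful even if the list is already fixed.
2. State how the list was built. If it is not yet in use, stratify it by training level in permuted blocks. With four arms and blocks of four, each complete block puts one participant in each arm, so arms differ by at most 1 within a stratum.
3. Use one population definition in the title, the aim and the eligibility criteria, and limit the minimum-dose conclusion to the population actually enrolled.

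The cost is one model degree of freedom for the training factor (and one for baseline torque), a second list to administer, possibly a few incomplete blocks, and a narrower conclusion. The sample size does not change.

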### Experimental procedure

A test-retest design with two measurement days and a 3-week, home-based, core-specific sensorimotor intervention is performed after the randomization procedure. The control group performs a standard intervention program as well. All test procedures are performed identically on both measurement days (M1 = prior; M2 = post intervention) in a standardized order. After assessing the anthropometrics (height, weight), a medical check-up is conducted to ensure that all participants are suitable for the upcoming trunk-strength testing. Participants are then prepared for surface electromyographic measurements (EMG) of the trunk. Twelve pairs of EMG electrodes are positioned over the ventral and dorsal muscles (Fig. 3; [4]). All participants undergo a general physical warm-up of at least 5 min prior to testing. Subsequently, a trunk-strength protocol, including isometric maximum voluntary contraction (MVC), isokinetic and sudden trunk loading for rotation as well as flexion and extension testing, is applied by an isokinetic dynamometer (CON-TREX MJ/TP, Physiomed AG, Schnaittach, Germany). The MVC measurement is used as a reference for the EMG-normalization procedure (Fig. 4). Subjective rating of load-induced back pain is assessed directly before and after the trunk-loading protocol (Visual Analog Scale VAS: 0.0–10.0 cm) to control for possible pain effects [13, 14].

